#### Primary safety outcome

The primary safety endpoints in the intervention group are any complications arising from the additional use of NPWT devices and the requirement for subsequent acute or subacute reintervention (at any time) as a result of the primary intervention.

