### Randomization

Following the consent process, eligible patients will be enrolled in the study through the online randomization system at the time of surgery in the operating theatre. Randomization will be on a one-to-one basis using a computer randomization program, with balanced allocation of patients across the two treatment groups, stratified by trial centre. All monitoring operating theatres can provide immediate internet access permitting the use of a secure 24-hour web-based randomization system to generate treatment allocation during surgery. Final eligibility will be confirmed by the treating surgeon at the end of the operative procedure before the wound dressing is applied, as a small subset of patients may be deemed clinically inappropriate for wound closure. A unique trial number will be assigned to each individual at the time of randomization. Patients will be randomized to one of two groups. There will be no sham intervention.

Group 1: single-use NPWT device applied to the closed skin incision after amputation.

Group 2: standard dry dressing applied to the closed skin incision after amputation.

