#### Standard dressing

Standard dressing for an amputation wound comprises a non-adhesive layer applied directly to the wound, covered by a sealed dressing, supplemented with protective padding. Such standard dressings do not use negative pressure. The precise details of the materials used will be at the discretion of the treating surgeon as per their routine practice but the details of each dressing applied in the trial will be noted. The duration that each dry dressing is left *in situ* varies between surgeons, though the majority will leave the first dressing for a minimum of 48 hours and a maximum of 5 days. For the purpose of this trial, the type and duration of control dressing will be recorded, including the postoperative day the dressing was first removed.

Of note, it is some surgeons’ usual practice to use a drain in the amputation stump delivered out through a separate incision to protect against haematoma formation; the drain is usually ready for removal at 48–72 hours after surgery. There is a lack of high-quality evidence supporting drain use after major amputation; however, it a widespread practice. Achieving a durable seal for NPWT around a drain can be technically challenging, and a seal may be lost once the drain is removed; extra care should be taken to maintain a seal once the drain is removed. For the purpose of this study, surgeons should not alter their regular practice regarding drain use. The presence or absence of a wound drain will be recorded in the procedural data, allowing for potential subanalysis of the impact of drain use on outcomes.

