### Device assessment

The single-use NPWT device will be reviewed daily by the surgical team and issues with sealing and exudate will be recorded. The number of devices left *in situ* sealed appropriately for the recommended period (minimum 5 and maximum 7 days) will be noted. All episodes of resealing on the ward will be documented. Reasons for premature removal of the NPWT device will be recorded.

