### Crossovers

Any crossovers between treatment groups shall be highlighted and reported in the final report. Participants’ follow-up data will continued to be recorded on an intention-to-treat basis, as such patients will continue to be analysed in the group they were originally randomized to whether they received the correct intervention or not. Reasons for protocol deviation will be documented in the site logs, for example NPWT device unavailable or unable to achieve seal despite multiple attempts or surgeon preference. Patients in the control group with unhealed wounds after the initial 14-day review period for whom the treating surgeon feels may benefit from application of a single-use NPWT device will be offered one.

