## Safety parameters

### Potential adverse events related to intervention

Primary safety endpoints include adverse events related to the use of single-use NPWT devices. The risk of any significant adverse event occurring is deemed unlikely; however, all reasonable measures to avoid these events will be undertaken. Any adverse events will be recorded and reported in any trial data, namely local reactions to the NPWT device.

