Use of randomization by stratification should ensure balance in the recruiting centre in both treatment groups. Whereas clustering effects are not expected to be important for this study, in reality the data may be hierarchical, with patients naturally clustered into groups by recruiting centre. This will be accounted for by generalizing the conventional linear (fixed-effects) regression approach to a mixed-effects logistic regression analysis. This model will be used to assess differences in wound complication rates between the study intervention groups, with results presented as odds ratios with associated 95% confidence intervals. The mixed-effects model will include a random effect to account for any heterogeneity in response due to the recruitment centre and fixed effects to adjust for vascular status. An identically structured and formulated mixed-effects linear regression model will be used to assess the effects of the interventions on secondary outcomes and EQ-5D-5L (at 1, 3, and 6 months) that, for the purposes of analysis, will be assumed to be approximately normally distributed. Other dichotomous outcome variables, such as complications related to the trial interventions, will be analysed in the same manner as the primary outcome. Temporal patterns of any complications will be presented graphically, and, if appropriate, a time-to-event analysis (Kaplan–Meier survival analysis) will be used to assess the overall risk and risk within individual classes of complications. All reported tests will be two-sided and considered to provide evidence for a significant difference if *P*-values are less than 0.05 (5% significance level. Results from this trial will also be compared with results from other trials and reported in accordance with CONSORT guidelines. Whereas there are a multiplicity of secondary outcomes, considering CONSORT guidelines and regulatory body preferences, the authors do not plan to adjust for type 1 errors due to the high risk of a corresponding increase in type 2 errors^22^.

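### The between-arm odds-ratio model is assigned to intervention-related complications, but the only ones defined and collected are NPWT-device complications, which a control patient without a device cannot have

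*Protocol article*

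**What the plan says.** Four parts of the protocol article bear on this point.

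- **Definition.** Under Primary safety outcome: "The primary safety endpoints in the intervention group are any complications arising from the additional use of NPWT devices". A second component is reintervention resulting from the primary intervention.
- **Collection, NPWT.** Under Device assessment: "The single-use NPWT device will be reviewed daily by the surgical team and issues with sealing and exudate will be recorded". Under Potential adverse events related to intervention: "Any adverse events will be recorded and reported in any trial data, namely local reactions to the NPWT device".
- **Collection, control.** Under Standard dressing: "the type and duration of control dressing will be recorded, including the postoperative day the dressing was first removed". No complication of the dry dressing is named there. Under Randomization: "There will be no sham intervention".
- **Analysis.** Under Statistical analysis, the primary model is a mixed-effects logistic regression with a random centre effect and adjustment for vascular status: "This model will be used to assess differences in wound complication rates between the study intervention groups, with results presented as odds ratios". The same section then adds: "Other dichotomous outcome variables, such as complications related to the trial interventions, will be analysed in the same manner as the primary outcome".

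The Crossovers section fixes the population: "patients will continue to be analysed in the group they were originally randomized to whether they received the correct intervention or not". It also lets controls whose wounds are unhealed after the 14-day review period be offered a single-use NPWT device. No one-arm analysis of device complications is stated.

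**The concern.** An odds ratio between arms is informative about safety when the event can arise, and is looked for, in both arms. A local reaction to a device, or a failed seal, needs a device. In a control arm without devices the count is zero by construction, and the model has nothing to estimate. If some controls receive a device and are analysed as randomized, the model may return a number, but that number depends chiefly on how many controls were exposed. The offer after day 14 goes to patients with unhealed wounds, so control-arm healing also feeds into it.

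At stake is the reporting of one component of the primary safety outcome. A large odds ratio with a small p-value could be read as evidence that the device is harmful, when it would arise even if the device carried the same risk in every patient who wore it.

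**Working it through.** **Inputs from the article.** The Sample size section gives 25% versus 15%, 90% power, a 5% level, 331 per arm, 10% added, 728 in total. Testing is two-sided.

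**The plan's own figure.** With the unpooled two-proportion formula, n = (0.25 × 0.75 + 0.15 × 0.85) × (1.960 + 1.282)² / 0.10² = 331 per arm. Then 331 × 1.1 × 2 = 728.2, so 728 reproduces and each arm has 728 / 2 = 364. The article states no figure for device complications.

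**Assumptions.** Let r be the complication rate per patient with a device, equal in both arms: 2%, 5% or 10%. Let f be the share of controls who receive a device: 0%, 5%, 10% or 20%. Every NPWT-arm patient is taken to receive one.

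**Case 1, f = 0.** At r = 5%, expect 364 × 0.05 = 18.2 events, taken as 18/364 versus 0/364. I used the planned model form, assuming eight centres and a binary vascular status split 50:50. The profile log-likelihood at fixed log odds ratios is:

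| Log odds ratio | Log-likelihood |
|---|---|
| 2 | -73.679 |
| 4 | -71.636 |
| 6 | -71.338 |
| 8 | -71.298 |
| 10 | -71.2920 |
| 15 | -71.29113 |
| 20 | -71.29113 |

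It flattens but has no maximum; at 20 it is still rising beyond the digits shown. A simpler logistic fit with arm only, at 17/331 versus 0/331, behaves the same way. After 5, 10, 20 and 30 iterations the log odds ratio is 3.65, 8.65, 18.65 and 28.65, with standard errors 0.92, 10.8, 1,610 and 238,000.

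**Case 2, f > 0.** The NPWT-arm rate is r and the control rate is r × f, so

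OR = [r / (1 − r)] / [rf / (1 − rf)] = (1/f) × (1 − rf) / (1 − r).

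The last factor is close to 1 for small r, so the odds ratio is about 1/f.

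| f | r = 2% | r = 5% | r = 10% | Expected control events (r = 5%) | P(no control event) (r = 5%) |
|---|---|---|---|---|---|
| 5% | 20.4 | 21.0 | 22.1 | 0.9 | 0.40 |
| 10% | 10.2 | 10.5 | 11.0 | 1.8 | 0.16 |
| 20% | 5.1 | 5.2 | 5.4 | 3.6 | 0.03 |

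The last two columns are 364 × rf and (1 − rf)^364. Reading across, a fivefold change in device risk hardly moves the odds ratio. Reading down, the crossover share sets it.

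**Example, r = 5% and f = 10%.** Taking 18/364 versus 2/364, OR = (18/346) / (2/362) = 9.4. The standard error of the log odds ratio is √(1/18 + 1/346 + 1/2 + 1/362) = 0.749, so the unadjusted 95% interval is 2.2 to 40.9, p = 0.003. This arises with identical risk per wearer. In the same scenario there is a 16% chance of no control event, which returns to Case 1.

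**The alternative summary.** One-arm reporting stays usable: 18/364 = 4.9%, exact 95% interval 3.0% to 7.7%; for 0/364 the upper limit is 1.0%.

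**The case against.** The strongest reply is that the Statistical analysis sentence names neither the device nor the primary safety outcome. It speaks of interventions in the plural, and the Interventions section describes both dressings. It could mean complications of either dressing, or binary outcomes counted by arm such as SSI and dehiscence. The definition and collection sections, which place device events in the intervention group and speak of recording and reporting them, already fit a one-arm description. An unseen case report form or analysis plan may settle the rest.

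Part of this stands. The wording is ambiguous, so the point rests on the most natural reading and not on an explicit instruction. But SSI and dehiscence are components of the wound composite, not complications of a dressing, and the article names no dry-dressing complication. Nor is the point an omission: a method is stated, and it does not suit the only endpoint that matches its description.

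It is also argued that with crossovers the odds ratio remains a valid contrast by allocation. That stands. A reader might infer that the estimate would be invalid or carry no information. The article does not support that: being allocated to NPWT does bring more device events, because more patients wear one. What the estimate cannot give is safety per wearer.

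**Conclusion.** The point holds as a minor correction. On the most natural reading, the stated model misfits the device-complication component of the primary safety outcome: there is no finite odds ratio without exposed controls, and about 1 divided by the exposed share with them. A penalized or exact method would return a finite number in the first case, but still no meaningful comparison.

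The sizes rest on assumed device rates (2% to 10%), assumed crossover shares (5% to 20%), equal risk per wearer, and a device for every NPWT-arm patient. The direction does not depend on the particular values, because the 1/f relation holds for any small r.

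A reader might infer that the whole primary safety outcome, or the trial's main comparison, is compromised. The article does not support this. Reoperations and readmissions are counted in each arm under Secondary outcomes, so the reintervention component can be compared, and neither the efficacy analysis nor the sample size uses device complications. Nor should one infer that controls are exposed only after day 14: the Crossovers section also foresees protocol deviations, so exposure can begin earlier.

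**What to change.** In Statistical analysis, state that NPWT-device complications are excluded from the between-arm model. Report them without an odds ratio or p-value, as n/N with an exact 95% confidence interval, where N is the number of NPWT-arm patients who actually received a device. List device events in controls who received one, by either route, separately with their own N. Keep the mixed-effects logistic model for events counted alike in both arms: reoperations, readmissions, SSI and dehiscence.

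This is a change of wording and needs no new data. The cost is that device safety is described and not compared. If the sponsor does want a comparison of dressing-related events, the alternative is to define and collect them in the same way in both arms, which means changing the safety definition and the control-dressing data collection.

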**Methods:**

This protocol describes a prospective, multicentre, randomized controlled trial with an internal pilot recruiting patients undergoing major lower extremity amputation for any indication. Limbs will be randomized to receive either a single-use NPWT device on their closed surgical incision or a dry dressing. The primary clinical outcome is the rate of wound complications. Secondary outcomes include reoperation rates, length of hospital stay, cost-effectiveness of NPWT, and patient-reported quality of life. Follow-up will continue to 6 months after surgery. The initial pilot phase has a recruitment target of 96 limbs, whereas an estimated 728 patients will be required to power a definitive trial adequately.

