## Background

Major lower extremity amputations are frequently performed for unreconstructable peripheral arterial disease and progressive diabetic foot complications^1,2^. As the population ages and the prevalence of diabetes increases, rates of diabetic-related major amputations are projected to increase despite advancing revascularization techniques. In both the UK and Ireland, rates of major amputation are significantly higher in the diabetic population^3,4^. In the United States, approximately 185 000 major amputations are performed annually, and the number of patients living with limb loss is projected to double from 1.5 million to 3.6 million by 2050^5^. Up to one-third of patients experience perioperative wound complications after major amputation^6–10^. Conversion from below-knee amputation (BKA) to above-knee amputation (AKA) is estimated to occur in 12–34% of limbs, with wound infection causative in a significant number of cases^8^. The 30-day readmission rate after a lower extremity amputation ranges from 29 to 46%^9,11^. Prolonged inpatient stays, multiple procedures, costly comorbidities, and high rates of readmissions lead to patients with peripheral arterial disease accumulating hospital costs six times those of general inpatients^12^. Similarly, the healthcare costs and resource utilization of diabetic foot care in England is greater than the combined cost of breast, prostate, and lung cancers^13^.

Many factors influence the risk of wound complications^14–18^. Notably, the presence of proximal occlusive arterial disease is a major influence on stump healing. Patient factors such as smoking, diabetes, obesity, malnutrition, and chronic kidney disease are non-modifiable, particularly in the emergency setting. However, surgical factors may be altered in an effort to reduce the risk of wound complications. One variable amenable to alteration is what dressing is applied to the closed incision upon procedure completion. The type of dressing may influence factors such as bacterial access to the wound, the development of collections of blood or fluid within the wound bed, or discharging onto the wound edges. Collectively, these wound factors increase the risk of wound infection. Therefore, dressings that reduce these factors have the potential to reduce wound breakdown, thereby reducing the burden for patients and healthcare systems.

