### Outcomes

#### Primary efficacy outcome

The primary outcome measure is any wound complication of the amputation stump, including SSI, dehiscence, seroma, haematoma, and stump necrosis. The Centre for Disease Control and Prevention^14^ definitions of SSI will be used (*Appendix 1*). As part of trial on-boarding, the Centres for Disease Control and Prevention (CDC) criteria for SSI will be shared to all clinicians involved in patient assessment. The treating clinical team will make the diagnosis of wound infection, as per routine clinical practice. Given that prompt diagnosis and treatment of wound infection is a core part of routine clinical care, the treating clinicians will typically document such a management change in the patients’ medical records. In addition, an independent outcome assessor will review data collected in the clinical report forms to confirm the diagnosis of a wound complication. For the purposes of the trial, any wound infection requiring ongoing medical intervention or that has led to reoperation at or after 30-day review will be considered a deep infection. Furthermore, any dehiscence involving the fascia or requiring interposition vacuum-assisted closure (VAC) therapy will be considered a deep dehiscence. Similarly, any stump necrosis involving the fascia or deeper structures will be considered deep necrosis, whereas superficial necrosis will be confined to the skin and subcutaneous tissues.

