#### Secondary outcomes

The secondary outcome measures comparing standard dressings to NPWT dressings in this trial are:

Number of recruited patients within the internal pilot will be assessed;Number of all wound complications (composite) in each arm will be collected;Number of SSIs in each arm will be assessed: any SSI meeting the CDC criteria will be documented and described as superficial or deep;Number of wound dehiscence rates in each arm within 6 months of index surgery will be assessed: any wound dehiscence will be documented and described as superficial or deep;Number of days to discharge for each arm will be assessed: the length of time the patient is in hospital from date of surgery to both the date of discharge and the date that the patient is deemed medically fit for discharge will be recorded;Number of reoperations within 6 months of index surgery in each arm will be assessed: any reoperations undertaken will be recorded;Number of readmissions to hospital within 6 months of index surgery in each arm will be assessed: all readmissions to hospital related to the surgical procedure will be recorded;Impact on quality of life: the EuroQoL EQ-5D-5L questionnaire is a validated measure of health-related quality of life. It comprises a five-dimension health status classification system and a separate visual analogue scale;Differences in wound-related quality of life in the 6 months following major amputation will be captured using the Wound-QoL questionnaire;Economic impact: the financial impact of patients’ out-of-pocket expenses will be recorded using the validated CoPaQ questionnaire. Patient self-reported information on service use has been shown to be accurate^11^. Healthcare resource use will be recorded for the economic analysis. Unit cost data will be obtained from national databases where available but where not available the unit cost will be estimated in consultation with the hospital finance department;Resource use and cost-effectiveness data, including number of NPWT devices utilized and troubleshooting with NPWT devices.

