### Definition of serious adverse event

Any event that results in death, a life-threatening adverse event, inpatient hospitalization or prolongation of existing hospitalization, a persistent or significant incapacity or substantial disruption of the ability to conduct normal life functions, or a congenital anomaly/birth defect is deemed a serious adverse event.

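### If the optional time-to-event analysis is run, Kaplan–Meier will overstate the absolute risk of wound complications, because death and higher-level re-amputation are competing events

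*Protocol article*

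**What the plan says.** The Statistical analysis section of the protocol article first plans a graphical display of when complications occur. It then says that, where judged appropriate, "a time-to-event analysis (Kaplan–Meier survival analysis) will be used to assess the overall risk and risk within individual classes of complications". Kaplan–Meier is the only estimator named, and it is named for both the overall and the class-specific risk. Whether the analysis is run at all is left open.

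The classes are those of the primary outcome: "any wound complication of the amputation stump, including SSI, dehiscence, seroma, haematoma, and stump necrosis". The Abstract sets the horizon: "Follow-up will continue to 6 months after surgery".

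The article recognises both events that can end a stump's time at risk:

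- **Re-amputation.** The Background says that conversion from below-knee to above-knee level "is estimated to occur in 12–34% of limbs, with wound infection causative in a significant number of cases". Under Secondary outcomes, "Number of reoperations within 6 months of index surgery in each arm will be assessed".
- **Death.** It appears in the definition of a serious adverse event: "Any event that results in death, a life-threatening adverse event". No mortality rate is given.

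The article does not mention competing risks or cumulative incidence functions, and does not say how death or re-amputation enters this analysis.

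**The concern.** The stated aim is to assess risk, meaning the proportion of patients who will have a given complication by a given time. Kaplan–Meier answers that question only if those censored could still have the event later, at the same rate as those still followed. A patient who has died cannot later have a first dehiscence, and a stump that has been removed cannot later become necrotic. Censoring them lets the remaining patients stand in for people who are no longer at risk, so the curve climbs too high.

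At stake are the absolute risks read from these curves. The article plans to compare its results with other trials, and a class risk taken from 1−KM is not comparable with one computed as a simple proportion. It could also disagree with the article's own counts. Dehiscence, for example, is to be counted per arm to 6 months, and that count keeps patients who die in the denominator.

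**Working it through.** **The plan's own figures.** The article states no figure for the time-to-event analysis. Its sample size reproduces and does not depend on this point: (1.960 + 1.282)² × (0.25×0.75 + 0.15×0.85) / 0.10² = 330.98, so 331 per arm; 331 × 1.10 × 2 = 728.2, so 728.

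**Inputs.**
- True cumulative incidence F by the end of follow-up: 25%, the article's assumed control rate for any complication, used here only as a scale; and 10%, an assumed single-class risk.
- Proportion C with death or higher-level re-amputation before the complication: not in the article, so assumed at 5%, 10%, 20% and 30%.

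**Scenario A, constant hazards.** The total cumulative hazard is H = −ln(1 − F − C). The complication's share is h = H × F/(F + C). Censoring the competing events gives 1−KM = 1 − exp(−h).

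Example with F = 10%, C = 20%: H = −ln(0.70) = 0.3567; h = 0.3567 × 0.10/0.30 = 0.1189; 1 − exp(−0.1189) = 11.2%, against a true 10%.

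**Scenario B, early complications.** 80% of complications are spread evenly over days 1–30 and the rest over days 31–180. Competing events are spread evenly over 180 days. Each day the Kaplan–Meier estimate is multiplied by 1 − a/S, where a is that day's complications and S the proportion still free of both events.

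Values of 1−KM, with relative excess in brackets:

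| Assumed C | A, true 10% | A, true 25% | B, true 10% | B, true 25% |
|---|---|---|---|---|
| 5% | 10.3% (3%) | 25.7% (3%) | 10.1% (1%) | 25.3% (1%) |
| 10% | 10.6% (6%) | 26.5% (6%) | 10.2% (2%) | 25.6% (2%) |
| 20% | 11.2% (12%) | 28.3% (13%) | 10.4% (4%) | 26.2% (5%) |
| 30% | 12.0% (20%) | 30.4% (22%) | 10.7% (7%) | 27.0% (8%) |

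Aalen–Johansen cumulative incidence returns the true 10% or 25% in every row.

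**Between arms.** Take true risks of 25% and 15%, with the same C in both arms, under scenario A. At C = 10%, 1−KM is 26.5% against 15.9%: the difference is 10.6 points instead of 10, and the ratio is 0.599 instead of 0.600. At C = 30% it is 30.4% against 18.1%: a difference of 12.4 points and a ratio of 0.594.

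**The case against.** The strongest reply is that this is a conditional, supplementary description in a journal article. The main analysis is a mixed-effects logistic regression of the 30-day proportion, other dichotomous outcomes follow the same route, and infections and dehiscence are also counted per arm. None of that uses Kaplan–Meier. Nor does the article say that deaths will be censored; a full analysis plan might handle them otherwise. The first part stands and limits the weight of the point. The second does not remove it: the article names an estimator for class risk, and censoring at death is how that estimator is ordinarily applied.

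A reader might infer more than the article supports:

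- **That 12–34% is the competing-event rate.** It covers below-knee to above-knee conversion only, has no time window, and the trial also enrols through-knee and above-knee amputations. The same sentence attributes a significant number of conversions to infection. A conversion that follows an infection does not compete with that infection, nor with the overall complication outcome.
- **That class risks summing to more than the overall risk would show the bias.** One stump can be both infected and dehisced, so correct class risks can also sum to more than the composite.
- **That the comparison of arms is distorted.** This would need competing rates that differ by arm, for which the article offers no figure.

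**Conclusion.** The point holds as a fault in a named method for a secondary, optional analysis. The direction is certain once some deaths or re-amputations occur before the time at which others have the complication and are censored: 1−KM then exceeds the cumulative incidence. Death affects every class. Re-amputation affects mainly the classes that did not cause it.

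The size rests on assumptions about frequency and timing that the article does not supply. For 5–30% competing events, the relative overstatement is about 3–22% under constant hazards and about 1–8% when most complications come early. In absolute terms, a 10% class risk would be overstated by at most about 2 points in the first case and 0.7 points in the second. If nearly all complications precede the competing events, the excess is negligible. Ratios between arms change little if competing rates are similar; absolute risks and differences change more. The primary result and the sample size are not touched.

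**What to change.** In the Statistical analysis section, replace Kaplan–Meier as the risk estimator. For example: if a time-to-event analysis is carried out, the overall risk and the risk of each complication class will be reported by arm as Aalen–Johansen cumulative incidence, with death and re-amputation of the index stump at a higher level as competing events.

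Confirm that the case report form captures the date of death and the date and level of any re-amputation. The article says that reoperations are recorded, but not explicitly that these dates are collected.

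The cost is a little more analysis work and possibly a package other than the SPSS version named. Recruitment, follow-up, the primary analysis and the sample size stay as they are, and the change can be settled before unblinding.
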